### Interventions

2.4

#### Responsive aggression regulation therapy

2.4.1

Re-ART is a protocolized intervention designed for (young) adults facing significant challenges with emotional and/or instrumental aggression regulation, and who exhibit a moderate to high recidivism risk. Incorporating the RNR principles (Andrews and Bonta, 2017), Re-ART demonstrates its flexibility by adapting the duration of the intervention (individual and group modules) according to the risk level, ranging from half a year to approximately 2 years (Risk principle). Additionally, it customizes treatment components based on the individual’s specific criminogenic issues (Needs principle), and tailors the intervention to the patient’s intelligence, learning style, pace, and preferred learning methods, among other factors (Responsivity principle).

The Re-ART treatment comprises standard modules, including Start, Network, Controlling Skills and Influence of Thinking. Optional modules, such as Stress Reduction, Impulse Control, Emotion Regulation, Observation and Interpretation, Self-Image and module for family systems, offer additional customization.

A comprehensive theoretical and program manual (Hoogsteder and Bogaerts, 2018) provide guidelines for each module, detailing the exercises and components to be included, along with the specific objectives that must be accomplished before progressing to the subsequent module. Moreover, the manuals outline the effective therapeutic techniques aimed at diminishing undesirable behaviors and fostering more desirable behaviors. These include motivational techniques to bolster patients’ self-belief and motivation to change, the aggression chain, psychoeducation to raise awareness of the negative consequences of aggressive behavior, exercises to manage and reduce negative emotions and interventions to identify and change irrational thoughts. The intervention also encourages patients to consider alternate perspectives by adopting the viewpoint of others with more facilitative ways of thinking.

Patient engagement in Re-ART consists of individual sessions occurring at least once a week, lasting for a minimum of 1 h. Depending on the risk level, more sessions per week can take place. Group training can take place, but the focus predominantly lies on individual treatment.

The current study focuses on measuring the effect of the Controlling Skills, Influence of Thinking and Handling Conflicts modules, which are offered in that order and usually last about 3–6 months. The Controlling Skills module focuses on learning control methods, to help individuals take a time-out more easily or stay calm when a time-out is not feasible, and to apply these methods in practice. The Influence of Thinking module focuses on reducing distorting cognitions and applying helping thoughts during difficult situations. The Handling Conflicts module aims to teach various skills necessary to handle conflict constructively, such as communicating appropriately, dealing with authorities and dealing with criticism.

#### Responsive aggression regulation therapy with virtual reality

2.4.2

In the Re-ART VR condition, identical modules (Controlling Skills, Influence of Thinking and Handling Conflicts) with the same exercises and role plays are provided, utilizing VR. For example, situations that provoke anger are simulated, allowing patients to practice skills aimed at preventing the escalation of aggression (e.g., applying a helpful thought or responding assertively rather than aggressively). In addition to exercises and role plays, the modules encompass various components, including psycho-education, mapping triggers, identifying dysfunctional cognitions and exploring conflict styles. To ensure that in the experimental condition VR is a substantial part of the treatment, it was determined that a minimum of 60 or 66% (depending on the module) of the sessions per module should be offered with VR. To monitor the attainment of this percentage, therapists fill out the Program Integrity checklist (see section 2.6.4.2).

Following the completion of the study, additional modules, including Impulse Control, Observation and Interpretation, Emotion Regulation and the Self-image module, can be made available if deemed necessary. This provision becomes applicable after the post-test measurement is conducted and extends to other interventions as well, such as pharmacotherapy and treatment of substance abuse. Moreover, the therapist, in collaboration with the patient, then has the flexibility to opt for VR treatment, irrespective of the study condition in which the patient was during the study.

### Criteria for discontinuing study participation

2.5

Participants who decide to discontinue participation in the study will receive a follow-up from their therapist to understand the reasons for their withdrawal. They will also have the option to be contacted directly by the main researcher. Feedback regarding the withdrawal will be sent via email to the main researcher to categorize responses for future discussion or reference. If any participant reports experiencing adverse effects or feels negatively impacted by their participation, they will be invited to a face-to-face meeting with the main researcher, therapist, and if necessary, a team leader. Additionally, participation in the study will be discontinued if, due to unforeseen circumstances during the study period, another intervention besides the three Re-ART modules must be provided.

#### Cyber sickness

2.5.1

Cyber sickness, also known as VR sickness or simulator sickness, is a common issue experienced by some individuals while using VR technology (Weech et al., 2019). Symptoms are like those of motion sickness, but they are less severe and less common (Kennedy et al., 1993). Cyber sickness occurs when there is a disconnect between the visual and vestibular systems, leading to sensory conflict and discomfort. Symptoms of cyber sickness include nausea or vomiting, dizziness, tired eyes, disorientation, dry mouth, sweating and problems with balance (LaViola, 2000; Davis et al., 2014). Some studies suggest that symptoms (at least partially) can be explained by overlap with anxiety symptoms (Fornells-Ambrojo et al., 2008). Therefore, it is expected that cyber sickness symptoms will decrease as anxiety symptoms decrease (Pot-Kolder et al., 2018). In case patients experience symptoms, such as dizziness or nausea, due to exposure to the VR environment, the therapist will help alleviate their discomfort. Several actions can be taken to prevent cyber sickness, such as building up the time a participant spends in the VR environment gradually and instruct the participant not to move his/her head too fast and in particular to walk straight (Rebenitsch, 2015). The main researcher provides a cyber sickness protocol, including instructions and strategies for therapists to prevent symptoms of cyber sickness. If cyber sickness symptoms persist and do not improve, the VR session will be halted, and a joint evaluation with the patient will determine the feasibility of continuing VR therapy. Should continuing VR therapy not be possible, the patient will be excluded from the study. Participants will be advised to seek a medical check-up with their general practitioner if any medical condition arises during the intervention period.

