### Study design

2.1

An RCT with a pretest-posttest design will be carried out in which forensic outpatient with aggression regulation problems are being assigned to either Re-ART using VR (Re-ART VR) or regular Re-ART. Pre- (prior to the Controlling Skills module—T1) and post-intervention (at the end of the Handling Conflicts module—T2) measurements are performed. Figure 1 presents the flow diagram.

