##### Impulsivity

2.6.2.2

From the FSI-R, the impulsivity subscale will be used to measure a general predisposition toward rapid, unplanned emotional (e.g., diminished ability to delay gratification) or behavioral (e.g., acting on the spur of the moment) reactions to internal or external stimuli without thinking about the consequences. The subscale contains four items (e.g., “I longed for more excitement”), each scored on a 5-point scale ranging from 1 “(almost) never” to 5 “(almost) always.” For reliability and validity data of the FSI-R, see section 2.6.1.1.

FSI-R and BITI are part of the standard Routine Outcome procedure in the forensic outpatient treatment center. Routine assessments of the FSI-R and BITI, which are typically conducted every 3–4 months, will sometimes be omitted if they closely coincided with pre- or post-treatment measurements. This is done to lessen the burden on patients participating in the study.

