#### Statistical analyses

2.7.1

The data analysis will be conducted using IBM SPSS v29. The analytical plan aims to examine the effectiveness of Re-ART with VR (Re-ART VR) compared to standard Re-ART in a forensic outpatient setting. Intention to Treat (ITT) analyses as well as Per Protocol (PP) analyses will be conducted. The ITT analyses will include data from all randomized patients, regardless of drop-out, whereas PP analyses will include only those patients who completed the treatment as originally allocated.

To evaluate treatment effects on primary and secondary outcomes, a Repeated Measures Analysis of Covariance (RM-ANCOVA) will be performed. This approach allows to account for both baseline scores and time, along with other potential covariates, thus providing a more precise estimation of the intervention effect.

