### Challenges

3.3

A key challenge is ensuring treatment fidelity across both the standard Re-ART and Re-ART VR conditions. Maintaining the integrity of the interventions and controlling for therapist variables could prove difficult. While not expected, cyber sickness could be an additional challenge that could affect the patient’s ability to complete the VR sessions (Weech et al., 2019). This could hinder the patient’s ability to complete VR sessions, necessitating withdrawal from the study. Additionally, technical issues and the need for continual software updates represent logistical challenges. To mitigate this, the research team maintains an ongoing collaboration with the VR-CBT software provider, CleVR, to ensure the utilization of up-to-date and optimally functioning VR sets and modules. Another challenge stems from the relatively early stages of VR adoption in clinical forensic practice. Implementation hurdles include therapists’ limited confidence and self-efficacy in using VR, along with practical resource constraints like time and technical support (Kouijzer et al., 2023). Therapists with limited VR experience in this study may hesitate to involve patients and may not fully realize its potential.

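### Two rules end study participation after randomization, one possible only in the VR arm, so the all-randomized ITT analysis would probably rest on imputed T2 outcomes for the patients removed

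*Protocol article*

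**What the plan says.** All references are to the protocol article.

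- **Section 2.5.1 (Cyber sickness)**, on symptoms that do not improve: "Should continuing VR therapy not be possible, the patient will be excluded from the study". Section 3.3 (Challenges) repeats the consequence: "This could hinder the patient’s ability to complete VR sessions, necessitating withdrawal from the study".
- **Section 2.5 (Criteria for discontinuing study participation)** has a second rule, worded without reference to arm. Under it, a patient's study participation ends when, unexpectedly, "another intervention besides the three Re-ART modules must be provided".
- **Section 2.1 (Study design)** places the post-intervention measurement "at the end of the Handling Conflicts module—T2".
- **Section 2.7.1 (Statistical analyses)** defines the two analysis sets: "The ITT analyses will include data from all randomized patients, regardless of drop-out", and "PP analyses will include only those patients who completed the treatment as originally allocated".
- **Section 2.7.1.1 (Preliminary analyses)** plans imputation for missing data.
- **Section 2.6.2.2 (Impulsivity)** notes that "FSI-R and BITI are part of the standard Routine Outcome procedure in the forensic outpatient treatment center". It gives the routine interval as 3–4 months and says routine assessments are sometimes omitted when they fall close to a study measurement.
- **Section 2.3.1 (Sample size)** requires 34 patients, 17 per arm, and makes no allowance for loss.

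**The concern.** Both rules act after randomization, and both end participation in the study, not only the allocated treatment. The first has no counterpart under regular Re-ART, so it can thin out only one arm. The second is triggered by a patient's clinical course during the study.

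ITT protects the comparison only if outcomes are sought from everyone randomized. If removed patients are not measured, the ITT set is complete in name but holds modelled values for these patients, and the missingness may differ between arms. With 17 per arm, a few such patients matter for the estimate and for power. A T2 that was never collected cannot be recovered at analysis.

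**Working it through.** **1. The sections read together.** Removal follows randomization (2.3.3, 2.5, 2.5.1). T2 falls at the end of Handling Conflicts (2.1), which a removed patient need not reach as a participant. Section 2.4.2 makes other interventions available after the post-test, so the second rule in 2.5 concerns patients who need one before T2. No section says that removed patients are measured at T2, and none says that they are not. The likely result is a missing T2 filled by imputation under 2.7.1.1.

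**2. The plan's own sample size.** Inputs from 2.3.1: f = 0.25, α = 0.05, power 0.80, 2 groups, 2 measurements (m = 2), correlation ρ = 0.5, ε = 1. For the within-between interaction:

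λ = f² × N × m / (1 − ρ) = 0.0625 × 34 × 2 / 0.5 = 8.5, with 1 and 32 degrees of freedom.

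The noncentral F distribution gives power 0.781 at N = 32 and 0.807 at N = 34. The stated 34 is reproduced.

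The same λ can be written as [n₁n₂/(n₁+n₂)] × D² / [2(1 − ρ)], where D is the between-arm difference in change in SD units. With 17 per arm, (17 × 17/34) × D² / 1 = 8.5 × D² = 8.5, so D = 1.0 SD.

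**3. Power after loss.** D stays at 1.0 SD and only the numbers with an observed T2 change. The loss counts are assumptions.

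| Patients lost | Power if all from VR | Power if that number is lost from each arm |
|---|---|---|
| 0 | 0.807 | 0.807 |
| 1 | 0.794 | 0.781 |
| 2 | 0.780 | 0.753 |
| 3 | 0.764 | 0.721 |
| 4 | 0.745 | 0.687 |

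The last column corresponds to total losses of 0, 2, 4, 6 and 8. One VR loss already brings power below 0.80.

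**4. Shift in a completers-only contrast.** Let q be the share of the VR arm removed, and g how much worse (in SD) their mean change would have been than that of retained VR patients. The full-arm VR mean is the retained mean minus q × g, so using retained patients only shifts the contrast by q × g. Positive values favour VR. Both q and g are assumptions.

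| Removed of 17 | g = −0.5 | g = 0 | g = 0.5 | g = 1.0 |
|---|---|---|---|---|
| 1 | −0.03 | 0 | +0.03 | +0.06 |
| 2 | −0.06 | 0 | +0.06 | +0.12 |
| 3 | −0.09 | 0 | +0.09 | +0.18 |
| 4 | −0.12 | 0 | +0.12 | +0.24 |

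For example, 4/17 × 1.0 = 0.235 and 4/17 × (−0.5) = −0.118.

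This table describes completers only. The planned ITT analysis imputes, and imputation reduces the shift only as far as the observed data explain the gap between removed and retained patients.

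**The case against.** The strongest reply is that the sections can be read together. Removed patients are drop-outs, the ITT set covers all randomized patients whether or not they drop out, missing values are imputed, and PP is defined separately. Figure 1, which gives the measurement overview, is not shown. Withdrawal reasons are categorised (2.5) and deviations recorded (2.6.4.2), so some drivers of missingness would be observed. Section 3.3 says cyber sickness is not expected, so the numbers may be small.

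Much of this stands, and it rules out three stronger readings that a reader might infer:

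- **That removed patients have no T2.** This is a strong inference from exclusion from the study and from the timing of T2, but it is not stated.
- **That the exclusion rules flatly contradict ITT.** Imputation allows a nominal all-randomized set. The weakness is that the set would rest on modelled outcomes for these patients.
- **That the rules bias the result toward VR.** Cyber sickness is described as a sensory conflict, not as failure of aggression regulation. Section 2.5.1 does link symptoms partly to anxiety and expects them to fall as anxiety falls, which makes poorer outcomes plausible but does not show them. The other-intervention rule covers both arms, so its effect could go either way or be nil.

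The reply does not supply a T2 for removed patients, and it does not alter the fact that one rule can operate in one arm only.

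**Conclusion.** The concern holds as a risk of differential missingness created by rules the article states. Followed as written, they would probably leave the ITT analysis relying on imputed outcomes for patients removed for treatment-related or clinical reasons.

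The direction of bias is not established. It plausibly favours VR under the cyber-sickness rule if those patients would have done worse, and it is uncertain under the other-intervention rule.

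The size depends on removal rates and outcome gaps that the article does not give. Over the assumed ranges, the completers-only shift stays at or below about a quarter of the 1.0 SD difference on which the trial is powered, and it may be zero or against VR. The power figures need no assumption about outcome gaps: there is no margin for loss, since the first missing VR patient takes the trial below its target. The point merits correction because it touches the primary comparison and is cheap to put right before outcomes are lost.

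**What to change.** Reconcile sections 2.5, 2.5.1 and 3.3 with section 2.7.1 by separating two events: stopping the allocated treatment and leaving the study.

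- A patient who stops VR or receives another intervention remains in the study unless he withdraws consent to the use of his data.
- Seek T2 FSI-R and BITI by a stated latest date, for example 6 months after T1, the upper end of the usual module duration in section 2.4.1.
- Use the routine FSI-R and BITI nearest that date as a fallback, and do not omit routine assessments for these patients.
- Analyse these patients in their allocated arm for ITT and exclude them only from PP.

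The cost is a change of wording, a T2 window and a small follow-up burden, since both questionnaires are already routine at the center. The ITT estimate will include the effect of other care received and may be slightly diluted. No change is proposed to the clinical decision on stopping VR or giving other care.

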### Materials

2.6

For an overview of the measurements (see Figure 1).

#### Primary outcome measurement

2.6.1

##### Degree of aggression regulation

2.6.1.1

The Forensic Symptoms Inventory-Revised Adults (FSI-R) (Van Horn, 2017) will be used to measure changes in the degree of aggression regulation. This self-report questionnaire consists of 32 items measuring eight domains of which a combined total score serves as a measure for the degree of aggression regulation: Aggression (e.g., “I threatened others”) and Anger (e.g., “I was annoyed”). Each subscale consists of four items, resulting in a combined scale of eight items that are rated on a 5-point scale ranging from 1 “(almost) never” to 5 “(almost) always.”

Higher scores on the subscales are indicative of increased deficits in cognitive, behavioral, and/or emotional functioning. The Aggression subscale assesses the extent of physical and verbal aggression. Patients with a high score on this subscale struggle to effectively manage their feelings of anger and rage, resulting in physical and/or verbal violence toward objects and/or individuals. The Anger subscale evaluates elevated levels of both direct and underlying anger. Patients with high anger scores may face an increased risk of aggressive impulse breakthroughs.

Multi-Group Confirmatory Factor Analyses supported the measurement and structural invariance with respect to gender and age groups (18–23 years and ≥ 24 years) (Van Horn, 2018) as well as longitudinal measurement invariance (Ten Hag, 2016). Reliability coefficients were in the acceptable to good range (α ≥ 0.68) for all subscales (Ten Hag, 2016; Mac Intosh, 2021).

#### Secondary outcome measurement

2.6.2

##### Cognitive biases

2.6.2.1

To assess cognitive biases, the Brief Irrational Thoughts Inventory (BITI) will be used (Hoogsteder et al., 2014b). The BITI is a self-report questionnaire comprising 16 statements that capture three types of irrational thoughts: Aggression and Justification (9 items, e.g., “If someone touches me, I should hit him”), Sub-Assertiveness (4 items, e.g., “I think that people get angry” with me because I often say “No”), and Distrust (3 items, e.g., “Everyone is against me”). Respondents rate each item on a six-point Likert scale, ranging from 1 “totally disagree” to 6 “totally agree.” The BITI’s construct validity is supported by convergent, divergent and concurrent validity evidence. Furthermore, measurement invariance was established across gender and ethnic origin (native versus non-native Dutch respondents) through confirmatory factor analysis, confirming the robustness of the BITI as a valid measure (Hoogsteder et al., 2014b). The list appears to be useful for adults as well. The BITI was also found to be measurement invariant for the background characteristics of age, sex, intellectual disability and migration background (Schoute, 2022).

##### Impulsivity

2.6.2.2

From the FSI-R, the impulsivity subscale will be used to measure a general predisposition toward rapid, unplanned emotional (e.g., diminished ability to delay gratification) or behavioral (e.g., acting on the spur of the moment) reactions to internal or external stimuli without thinking about the consequences. The subscale contains four items (e.g., “I longed for more excitement”), each scored on a 5-point scale ranging from 1 “(almost) never” to 5 “(almost) always.” For reliability and validity data of the FSI-R, see section 2.6.1.1.

FSI-R and BITI are part of the standard Routine Outcome procedure in the forensic outpatient treatment center. Routine assessments of the FSI-R and BITI, which are typically conducted every 3–4 months, will sometimes be omitted if they closely coincided with pre- or post-treatment measurements. This is done to lessen the burden on patients participating in the study.

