##### Primary outcome analysis: degree of aggression regulation

2.7.1.2

An RM-ANCOVA will be conducted with the FSI-R scores at both pre- and post-intervention as the within-subjects factor. The treatment condition (Re-ART VR vs. regular Re-ART) will serve as the between-subjects factor. Covariates like age, motivation level, and risk of recidivism will be included to control for initial differences.

The primary focus will be on the interaction term between treatment condition and time to examine whether the rate of improvement in aggression regulation differs between the two conditions.

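### The stated ITT analysis uses only T1 and T2, although routine FSI-R and BITI scores taken in between could inform the imputed outcomes of early leavers (minor)

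*Protocol article*

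**What the plan says.** All references are to the Protocol article.

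- **Timing of the study measurements (2.1 Study design).** T1 precedes the first of the three modules. T2 is taken "at the end of the Handling Conflicts module", so it is tied to completing the modules and not to a calendar date.
- **Length of the course (2.4.1).** The three modules are ones "which are offered in that order and usually last about 3–6 months".
- **Routine measurement (2.6.2.2 Impulsivity).** The centre collects the same two questionnaires as standard care: "Routine assessments of the FSI-R and BITI, which are typically conducted every 3–4 months", but these "will sometimes be omitted if they closely coincided with pre- or post-treatment measurements". The reason given is patient burden: "This is done to lessen the burden on patients participating in the study".
- **Analysis set (2.7.1).** "The ITT analyses will include data from all randomized patients, regardless of drop-out".
- **Model (2.7.1.2).** "An RM-ANCOVA will be conducted with the FSI-R scores at both pre- and post-intervention as the within-subjects factor". Section 2.7.1.3 does the same for the secondary outcomes. Section 2.7.1.1 says that missing data will be imputed but lists no predictors for the imputation.
- **Early exits (2.5 and 2.5.1).** Participation ends on withdrawal, when another intervention proves necessary, or when VR therapy cannot continue because of cyber sickness. No outcome measurement after these exits is described.

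**The concern.** A patient who stops before the last module does not reach the point at which T2 is defined, yet remains in the ITT analysis. Under the stated two-point model, that patient's T2 has to be imputed. T1 and baseline covariates carry no information on how the patient fared after treatment began. A routine FSI-R or BITI score taken during the modules does, on the same scale and at no extra collection cost. The article mentions these scores only to say that some will be left out.

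Two things are at stake. The first is precision, in a trial of 17 patients per arm with no stated allowance for drop-out. The second is how credible the missing-at-random assumption is. Some of the described exits could follow from the patient's state during treatment, and one of them (cyber sickness) can occur only in the VR arm. An intermediate score makes that assumption easier to defend.

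**Working it through.** **1. The plan's own figure.** Inputs from 2.3.1: f = 0.25, α = 0.05, two groups, m = 2 measurements, ρ = 0.5, N = 34. For the within-between interaction, λ = N·m·f²/(1 − ρ) = 34 × 2 × 0.0625/0.5 = 8.5 on 1 and 32 degrees of freedom. Power is 0.807. N = 32 gives 0.781, so 34 is reproduced. It is the number needed with complete data.

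**2. Planned effect on the SD scale.** With ρ = 0.5, the SD of change is √(2 × (1 − 0.5)) = 1.0 SD. The standard error of the difference in change is √(1/17 + 1/17) = 0.34 SD. The planned difference is √8.5 × 0.343 ≈ 1.0 SD.

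**3. How many routine scores can exist.** A course of 3–6 months with forms every 3–4 months yields between 3/4 = 0.75 and 6/3 = 2 routine dates. That is about one and at most two between T1 and T2. A patient who leaves before the first routine date has none.

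**4. What the omission rule can lose.** A form skipped near T1 loses nothing, because T1 is on file. A form skipped near T2 loses nothing if T2 is then completed. Data are lost only if the form is skipped and T2 then fails to arrive.

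**5. Information in one routine score.** The T1–T2 correlation of 0.5 is the plan's. The other correlations are assumptions. For a drop-out with such a score:

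- T1 only: R² = 0.5² = 0.25.
- T1 plus routine score, all correlations 0.5: R² = (0.25 + 0.25 − 2 × 0.5 × 0.5 × 0.5)/(1 − 0.25) = 0.25/0.75 = 0.333.
- T1 plus routine score, adjacent correlations 0.7: R² = (0.25 + 0.49 − 2 × 0.5 × 0.7 × 0.7)/(1 − 0.49) = 0.25/0.51 = 0.490.

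The partial correlations with T2 given T1 are √((0.333 − 0.25)/0.75) = 0.33 and √((0.490 − 0.25)/0.75) = 0.57.

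**6. Effect on power.** The documents give no drop-out rate, so 10%, 20% and 30% without T2 are assumed. Let n_c be the number with T2, n_d the number without, q the share of drop-outs with a routine score (0.25 to 1, assumed), and r the partial correlation (0.3 to 0.7, assumed). The approximate effective size is N_eff = 1/[(1 − r²)/n_c + r²/(n_c + q·n_d)], entered in the formula of step 1.

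| T2 missing | n_c | Power, completers only | Power with routine scores | Gain (points) |
|---|---|---|---|---|
| 10% | 30.6 | 0.762 | 0.763–0.784 | 0.1–2.2 |
| 20% | 27.2 | 0.708 | 0.710–0.755 | 0.2–4.7 |
| 30% | 23.8 | 0.645 | 0.649–0.720 | 0.4–7.5 |

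Each lower end has q = 0.25 and r = 0.3; each upper end has q = 1 and r = 0.7. The value r = 0.7 is above both partial correlations in step 5, so 7.5 points is an optimistic end.

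**7. Illustrative bias.** In a large-sample simulation, VR drop-out depended on the mid-treatment score and control drop-out did not. Imputing T2 from T1 alone gave a false VR benefit of 0.05 SD (25% VR drop-out, correlations 0.5), 0.08 SD (25%, adjacent correlations 0.7) or 0.13 SD (30%, stronger dependence). Adding the mid-treatment score brought it to within 0.005 of zero. Against step 2, 0.05–0.13 SD is 5–13% of the planned difference and about 0.15–0.38 standard errors.

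**The case against.** The strongest reply is that the article leaves less undone than it seems to.

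- **A reader might infer that the omission rule strips the trial of its mid-treatment scores.** It does not. It covers only forms that nearly duplicate T1 or T2, and step 4 leaves one narrow case of loss. This part of the reply stands.
- **A reader might infer that a drop-out's T2 will be reconstructed from T1 alone.** The article does not say so. Section 2.7.1.1 names no imputation predictors, and 2.7.1.2 names age, motivation level and recidivism risk as covariates. Auxiliary variables are commonly listed in an analysis plan, which is not shown, so silence on them is no fault. This also stands. What remains is that the analysis is stated as two-point, and that a form never taken cannot be recovered by a later plan.
- **A reader might infer that routine scores are the only outcome data a drop-out can leave.** Nothing forbids asking a drop-out for T2, and 2.5 provides for therapist contact after withdrawal. The supported statement is that routine scores are the only source after T1 that the article describes for such a patient.
- **The bias figure is partly built in.** The simulation lets drop-out depend on the mid-treatment score in one arm only, so conditioning on that score removes the bias by construction. It also assumes that every drop-out has the score. Neither assumption, nor the 25–30% rates, comes from the documents.

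**Conclusion.** The point holds as a minor improvement. ITT is claimed for all randomized patients, T2 depends on finishing the modules, and the stated models use two time points, while the centre already holds or could hold an intermediate score on the same scales for some early leavers.

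The benefit is modest and conditional. For a drop-out with a routine score, predictable T2 variance rises from 25% to 33–49%. Power rises by about 0.1 to 7.5 percentage points at an assumed 10–30% missing T2. Both ranges rest on assumed correlations and availability, and early leavers without a routine score gain nothing.

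The documents do not support the stronger conclusion that the trial will show a false VR benefit of 0.05–0.13 SD. That range shows what one assumed pattern of drop-out would do, and it is small beside the planned difference of about 1.0 SD.

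**What to change.** 1. **Section 2.7.1.** Add a sentence such as: *In the ITT analysis, routine FSI-R and BITI scores dated between T1 and T2 (for drop-outs, up to 6 months after T1) enter the imputation model, or a mixed model, as an extra dated measurement.* Six months is the upper end of the module duration in 2.4.1.
2. **Section 2.6.2.2.** Add: *A routine form due near T2 is skipped only once the completed T2 form has been received.* Patients who complete T2 are still spared the duplicate, so the burden argument is kept.

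The cost is linking scores from the centre's routine records to the study file, with their dates, and an occasional extra questionnaire. No new instrument or staff is needed. If the unseen analysis plan already uses the routine scores, only the second change remains.
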